## Abstract

**Background:**

In Norway, a disproportionately high number of children receiving Child Welfare Services (CWS) struggle academically and drop out of school. Academic attainment is one of the strongest protective factors against societal marginalization. The present study is part of a knowledge translation project in collaboration with local CWS with the aim to develop, implement, and evaluate Enhanced Academic Support (EAS) for primary school children in CWS.

**Methods/design:**

The study is a mixed-methods hybrid type 2 randomized, controlled pragmatic trial. The participants are approximately 120 children whose families receive support measures from three child welfare agencies in and around Oslo, Norway, and practitioners from these agencies. Families are randomly assigned to either the EAS condition or “business as usual” support. Primary outcomes are math and reading skills, parental involvement in school, and intervention fidelity. Questionnaires and academic tests are administered at baseline, post-intervention (after 6 months), and at follow-up (after 12 months). Implementation drivers are assessed before and after the trial period, and intervention fidelity is monitored during the trial through checklists and structured telephone interviews. Semi-structured interviews and focus groups are conducted after the trial.

**Discussion:**

This hybrid study has two implications. (1) The effects of providing EAS to children in child welfare will be investigated. The study also explores how each core component of the intervention and the use of specific adaptations, implementation drivers, and other important child-level covariates moderate the overall effects. The results can provide valuable knowledge about how to deliver precise and effective academic support to increase academic skills and prevent dropout. In turn, this can promote academic completion and well-being, outcomes that are beneficial for both children and society at large. (2) The study also evaluates the feasibility of applying an Integrated Knowledge Translation model designed to develop, implement, and evaluate research-supported practice in health, care, and welfare services in less time than is usually the case. If deemed successful, this model will provide an efficient collaborative approach to translate the best available evidence into effective evidence-based practice, applicable in effectiveness research and quality improvement efforts.

**Trial registration:**

ISRCTN, ISRCTN38968073. Registered on 18 September 2017. 10.1186/ISRCTN38968073.

**Electronic supplementary material:**

The online version of this article (10.1186/s13063-018-3079-4) contains supplementary material, which is available to authorized users.

## Background

### Translating knowledge into effective and sustained practice

The translation of knowledge from research into effective and sustained practice is a critical issue in health, care, and welfare systems [1]. More successful translational efforts will likely result in improved services for patients, clients, and users and less inadequate treatment and care [2]. Municipal health, care, and welfare services in Norway experience increasing demands to ensure safe and effective services of high quality. Steps toward meeting these demands likely include identification of factors that contribute to favorable outcomes, supply and translation of the best available knowledge, and the establishment of quality monitoring and feedback systems.

### Need for knowledge translation in Child Welfare Services

In Norway, the Child Welfare Services (CWS) need support to succeed in quality improvement endeavors. The majority (approximately 70%) of CWS is delivered by municipal agencies located across the country [3]. These agencies vary considerably in size and organizational structure. They differ in terms of methods of practice, approaches for quality improvement, and quality monitoring systems. Although a state-led body governs and serves the municipal CWS agencies, the responsibility for ensuring and improving quality of services rests with local municipal government and the agencies themselves. CWS agencies often juggle demanding directives, high caseloads, scarce resources, and a high rate of staff turnover. Their practitioners hold challenging jobs and are prone to stress and burnout [4]. The Norwegian Child Welfare Act, section 4-4 [5] states: “The child welfare service shall contribute to provide the individual child with sound circumstances and opportunities for development by providing advice, guidance and assistance.” To meet increasing demands to ensure safe, effective, and high-quality advice, guidance, and assistance, municipal child welfare agencies would benefit from professional support.

### Marginalization and academic achievement among children in child welfare

Contributing to a healthy upbringing is important in itself, but it is also a good investment socially and economically. As a group, children in families who receive CWS are at greater risk of developing mental health issues and behavioral and substance abuse problems, and are also at greater risk for future unemployment and engaging in criminal behavior [6].

Children in child welfare in Norway are more than twice as likely to drop out of school compared to their peers [7]. Only two in ten children who have been involved with CWS complete secondary school on schedule, and 35% are neither employed nor in education by the time they reach 23 years of age [7]. In comparison, six in ten children in the general population complete secondary school on time, and under 10% are neither employed nor in education at the age of 24 years [8]. Children in CWS are often found to have knowledge gaps very early on in their academic careers, deficits that over time grow bigger and frequently result in academic failure and dropout [9]. Additionally, individual factors such as mental health, social skills, and executive functioning are likely to affect these children’s ability to succeed academically [10, 11]. Academic achievement is one of the strongest protective factors against later marginalization [12, 13]. In a study of 7000 Swedish children with a history of foster care, academic achievement strongly predicted positive outcomes in adulthood (i.e., not being on welfare, and showing less illness, drug abuse, and criminal behavior), even when other factors such as socioeconomic status were controlled [9]. Most studies on the provision of academic support to children in the CWS have focused on children in foster care [14–16]. Recently published statistics in Norway, however, show that children involved with CWS who are living with their biological parents are at a similar risk of academic failure as children who are placed outside the home [7].

Practitioners in CWS have reported that the children in their care need more appropriate and tailored support to succeed academically [17]. However, child welfare agencies lack the methods, training, and allocated resources to provide academic support. Research has indicated that providing academic support to children and their families outside of school hours, and especially at home, has very useful potential [14, 15]. Meta-analyses have shown that positive parental involvement (e.g., homework support, parent-teacher communication, positive communication about school, positive parental expectations) affects children’s academic performance positively [18, 19]. A systematic review of out-of-school-time academic (OSTA) programs for children at risk of dropout in the USA found that reading- and math-focused OSTA programs can improve reading and math achievement [20]. The authors highlighted the need to combine OSTA programs with other educational, community, and family support to achieve sustained effects.

### Using Integrated Knowledge Translation to develop and evaluate academic support in child welfare

To support child welfare agencies in the development of appropriate academic support, the current project applied an Integrated Knowledge Translation (IKT) model in collaboration with three child welfare agencies. IKT is an approach to research that engages researchers and stakeholders (e.g., child welfare managers and practitioners, youth and parents with child welfare experience, and school personnel) in collaborative partnerships to exchange, create, and utilize knowledge to address research issues [21]. The IKT model applied in the present project has combined IKT principles with methods from quality improvement and innovations in knowledge synthesis (we have labeled our model IKT-K, to distinguish it from other knowledge translation approaches). IKT-K entails synthesizing the best available evidence and translating the evidence into locally tailored and flexible research-based practice. IKT-K is structured in five phases: synthesis, co-creation, implementation, evaluation, and sustainment or de-implementation. During the first three phases, a locally tailored academic support intervention (Enhanced Academic Support, EAS) was developed based on common elements of effective academic interventions. EAS was implemented in three child welfare agencies, and its effects on academic achievement and parental involvement will be evaluated in this randomized controlled trial. The trial also evaluates the quality of EAS implementation and feasibility of the IKT-K model.

### Aims and hypotheses

The present study has three overarching aims:To evaluate the feasibility of the IKT-K model designed to develop, implement, and evaluate empirically supported practice in CWSTo evaluate the effects of the intervention, EAS, on children in CWS and their familiesTo explore associations between implementation drivers (readiness, climate, fidelity) and outcomes for children and families.

The following research questions will be examined to evaluate Aim 1:To what degree are the core components of EAS implemented in the CWS?What adaptations are made to the core components of EAS?What are stakeholders’ perceptions of the IKT-K model’s feasibility and usefulness, as assessed in focus groups?To what degree are climate for implementing evidence-based practice (EBP) and susceptibility for change of practice (readiness for change) associated with intervention fidelity in the CWS?To what degree will practitioners in the experimental group increase their perceived competence in delivering academic support to children and families from pre- to post-intervention?To what degree is adherence to core components of EAS associated with academic achievement and parental involvement for families in the EAS group?

The following hypotheses will be tested to evaluate Aims 2 and 3:Children in families who receive the EAS intervention will improve their academic achievement relative to children and families in a parallel, active comparison group who receive “business as usual” (BAU) support.Parents who receive the EAS intervention will increase their engagement in their children’s school situation relative to parents who receive BAU.Intervention effects will be moderated by child age, readiness for change, and climate for implementing EBP.Covariates include children’s mental health, social skills, and executive functioning scores, as well as child gender and pre-intervention academic performance (math and reading) and parental involvement.Intervention effects (measured by academic performance tests and parental involvement) are associated with climate for implementing EBP and readiness for change.More adherence to EAS principles will be positively associated with academic achievement and parental involvement for families in the EAS group

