## Methods and design

This study is a randomized controlled pragmatic trial conducted in three ordinary child welfare agencies in and around Oslo, Norway. The agencies differ in size, organizational structure, and demographic characteristics. Selected practitioners at each site have received training in the EAS intervention. Practitioner selection to EAS training was mostly a matter of practicality (i.e., half of the practitioners in a team, geographic area, or unit were selected by their managers to receive training). Participating families are recruited individually at each site and randomized either to an EAS-trained practitioner or to a practitioner not trained in EAS who is delivering regular child welfare support measures (BAU). EAS is delivered over the course of 6 months. Participants are assessed before and immediately after EAS, and at follow-up, 6 months after the end of the intervention. The schedule of recruitment, allocation, assessments, and experimental conditions is provided in Fig. 1. The Standard Protocol Items: Recommendations for Interventional Trials (SPIRIT) checklist is provided as Additional file 1.

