#### Exclusion criteria

The exclusion criteria are as follows:Developmental disabilityParents/caregivers not able to give informed consent due to language restriction (not able to understand Norwegian, English, Arabic, or Somali)One child only from each family can participate

The study also includes managers and practitioners at the local child welfare agencies (*N* = 160), the children’s teachers, and other stakeholders (parents and youths who previously received CWS, youth from user organizations, and local school counselors; estimated *N* = 22) in and around Oslo, Norway.

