**Fig. 2 Fig2:**
[figure not shown]
Model of intervention effects, covariates, mediators, and moderators

Organizational readiness for change and organizational climate for implementing EBP are measured to inform the implementation process and to be tested as predictors in the implementation model (see Fig. 3).

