#### Implementation measures

The following implementation measures are used in this study:A monitoring checklist has been developed to measure adherence to core components, dosage, competence in delivery, parent comprehension of core components, adaptations, and user involvement and satisfaction with delivery of intervention components. The checklist is completed by EAS practitioners using smartphones after each intervention session and by parents answering the same questions in telephone interviews after each intervention session (see the section “Monitoring and safety” for more details).An end-of-intervention checklist measures academic support received/given, emergent life events/adverse events, and overall user satisfaction and involvement during the last 6 months (intervention period). It has been developed specifically for this study and is administered at the post-assessment to parents (15 items), children (16 items), and practitioners (20 items) in both conditions. Items are rated on a 4-point scale (“not at all”, “to a small degree”, “to some degree”, “to a large degree”). Each version ends with an open question about any additional information to be answered in free text.Intervention feasibility, acceptability, and appropriateness will be measured using three four-item scales: Acceptability of Intervention Measure (AIM), Intervention Appropriateness Measure (IAM), and Feasibility of Intervention Measure (FIM) [30]. The AIM, IAM, and FIM are completed by the EAS practitioners post-intervention.Organizational readiness for change is assessed using an unpublished questionnaire made by the study authors with 32 items rated on a 5-point scale (ranging from “strongly disagree”, “somewhat disagree”, “unsure”, “somewhat agree”, to “strongly agree”). The questionnaire measures organizational factors, characteristics, needs, and work climate as well as staff characteristics, qualities, and needs. It is administered to all employees at all CWS sites, pre- and post-intervention. Organizational managers answer two additional items measuring organizational resources and opportunities.Organizational climate for implementing evidence-based practice (EBP) is assessed using the Implementation Climate Scale (ICS) [31]. The scale consists of 18 items rated on a 5-point scale (from “not at all” to “very great extent”). The ICS assesses the degree to which there is a strategic organizational climate supportive of EBP implementation. Subscales include focus on EBP, educational support for EBP, recognition for EBP, rewards for EBP, selection (employment) for EBP, and selection (employment) for openness. The ICS is administered to all employees at all CWS sites pre- and post-intervention. It has been validated with practitioners in 32 mental health organizations and 12 child welfare services in the USA [31, 32].Practitioners’ perceived competence in providing academic support is measured using an unpublished questionnaire developed by the study authors. It includes 12 items rated on a 5-point scale ranging from “strongly disagree” (0) to strongly “agree” (5). The questionnaire assesses knowledge and use of competencies relevant to the core components of EAS without using the specific wording of the core components in the EAS handbook. It is administered pre-training and post- intervention to EAS practitioners.CWS employees’ perceptions of the implementation process and the EAS intervention will be gauged by conducting focus group interviews post-intervention. An interview protocol will be prepared based on the IKT-K model and the DAP framework, including questions about the appropriateness and acceptability of EAS. Some of the topics to be discussed in the focus groups will include results from the quantitative data analyses.Semi-structured interviews will be conducted with a selection of participating children and parents after the intervention to learn more about their experiences with EAS. To select families to approach for participation in interviews, a randomization procedure in the Confirmit software will be used. Randomization will be stratified to select families who benefited from the intervention, who did not benefit from the intervention, and families with different ethnicities from each of the three sites.

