### Statistical analyses

We will consider efficacy for each of the primary outcomes. In other words, efficacy will be gauged in an outcomes-specific manner. A significance level of .05 will be used.

Outcomes will be evaluated using analysis of covariance (ANCOVA), controlling for baseline scores and covariates. Children’s age, implementation drivers, children’s mental health, social skills, and executive functions will be tested in regression models, as will possible subgroup analyses. To test for indirect effects (or mediation), models will be tested in a structural equation modeling (SEM) framework. Indirect effects variables include PASS, Five-to-Fifteen , and the end-of-intervention checklist measures. Implementation drivers as predictors of outcomes will be tested in regression models. We will evaluate effectiveness in two parts. The pre-post outcome analysis will use ANCOVA with baseline measures and covariates as control variables. We will test intervention effects including all data waves in SEM. See Figs. 2 and 3 for the theory of intervention change depicting variables included in the analyses.

We will examine and present data both in intention-to-treat (ITT) and as-treated (AT) designs, as the two approaches answer different questions. An ITT design answers the question “Does the intervention make a difference?” An AT analysis, on the other hand, answers the question “What are the effects likely to be if the client (or family) is exposed to the intervention?” We consider both of these questions important. This procedure has been recommended as best practice [46].

We will use multiple imputation for missing values for the pre-post ANCOVA in an ITT design. In the SEM models, missing data will be estimated using full information maximum likelihood.

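### Readiness and climate are organizational constructs measured in only three agencies, so agency-level scores cannot support the planned moderation and association tests, and the protocol does not state the score level

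*Protocol article*

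**What the plan says.** Under Aims and hypotheses, the protocol article lists hypotheses that are to be tested for Aims 2 and 3. One reads: "Intervention effects will be moderated by child age, readiness for change, and climate for implementing EBP". A further one says that intervention effects are associated with climate and readiness. Aim 3 itself is worded as exploration and covers readiness, climate and fidelity.

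The number of organizations is given under Methods and design: "This study is a randomized controlled pragmatic trial conducted in three ordinary child welfare agencies in and around Oslo, Norway". The same paragraph says that the agencies differ in size, structure and demographics.

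Both drivers are labelled organizational. The Measures section states: "Organizational readiness for change and organizational climate for implementing EBP are measured to inform the implementation process", and adds that they will be tested as predictors. Implementation measures says: "Organizational readiness for change is assessed using an unpublished questionnaire made by the study authors with 32 items", and of the climate scale: "The ICS assesses the degree to which there is a strategic organizational climate supportive of EBP implementation". The answers come from individual staff: "The ICS is administered to all employees at all CWS sites pre- and post-intervention", and readiness is collected in the same way. The staff sample is 160 managers and practitioners (Exclusion criteria).

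On the model, Statistical analyses says: "Implementation drivers as predictors of outcomes will be tested in regression models". Drivers are listed there beside child age, mental health, social skills and executive functions. No agency, team or practitioner level is named, and nothing says whether the score entered is an agency mean, a team mean or the score of the family's own practitioner.

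**The concern.** A property of an organization can be studied only across organizations. With three agencies, an agency-level readiness or climate score takes three values, however many families are enrolled. A regression on 120 family rows nevertheless uses a standard error and a critical value suited to about 120 independent observations.

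The risk is that ordinary variation between three agencies is reported as evidence that climate or readiness drives the effect of EAS. That is the question Aim 3 is meant to inform. The agencies are stated to differ in other ways too, and with three of them these differences cannot be told apart from the drivers.

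**Working it through.** **Plan's own figure.** The only sample-size figure is 78 families (39 per group) for d = 0.65 and power 0.80. It reproduces: a two-sided t-test at 0.05 has power 0.799 with 38 per group and 0.809 with 39. (Alpha is printed in that section as below 0.5, but 78 is obtained only with 0.05, the level in Statistical analyses.) The figure concerns the EAS-versus-BAU comparison. No power or precision is given for the driver tests.

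**Inputs from the protocol.** Three agencies; 120 families; significance level 0.05; randomization of families within site.

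**Assumptions.** 40 families per agency with 20 per arm, two-sided testing, outcome SD of 1, and scores constant within agency. The between-agency SDs and intraclass correlations (ICC) below are assumed, because the protocol gives none.

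**Step 1: degrees of freedom with agency scores.** One driver fitted to three site-specific EAS effects uses an intercept and a slope, leaving 3 − 2 = 1 df. The two-sided 5% critical value is 12.7. Family-level regression with an arm-by-driver interaction has 120 − 4 = 116 df and a critical value of 1.98. Readiness and climate together use 3 parameters on 3 agencies, leaving 0 df, so they carry the same information as site indicators.

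**Step 2: interaction test.** The sampling variance of one agency's EAS-minus-BAU difference is v = 4/m = 4/40 = 0.10. Let τ be the between-agency SD of the EAS effect that the driver does not explain. The variance is inflated by 1 + τ²/v, and the actual type I error is 2[1 − Φ(1.96/√(1 + τ²/v))].

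| τ (assumed) | Inflation | Type I error, formula | Simulated |
|---|---|---|---|
| 0 | 1.0 | 5.0% | 5.2% |
| 0.1 | 1.1 | 6.2% | 6.1% |
| 0.2 | 1.4 | 9.8% | 9.4% |
| 0.3 | 1.9 | 15.5% | 15.0% |

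Agency differences in outcome level do not enter, because arms are compared within agency and those levels cancel.

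**Step 3: what a valid agency-level test could do.** The 1-df test held about 5% in the same simulations. Its power was about 8–9% for an assumed slope of 0.3 SD per score unit, with scores one unit apart.

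**Step 4: plain driver–outcome association.** Nothing cancels here. In the EAS arm (60 families, 20 per agency) the variance of an agency mean is 1/20 = 0.05, so the inflation is 1 + s²/0.05 for a between-agency SD s of outcome means.

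| s (assumed) | Inflation | Type I error, formula | Simulated |
|---|---|---|---|
| 0.1 | 1.2 | 7.4% | 7.0% |
| 0.2 | 1.8 | 14.4% | 13.2% |
| 0.3 | 2.8 | 24.1% | 22.9% |

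If all 120 families are used, the design effect is 1 + 39 × ICC. At ICC 0.01, 0.05 and 0.10 it is 1.39, 2.95 and 4.90, with type I error 9.6%, 25.4% and 37.6%. These figures do not include adjustment for baseline scores, which the protocol plans and which could shrink agency differences in outcome.

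**Step 5: practitioner or team scores.** There are then more than three values. Families sharing a practitioner or team share a score, so ordinary regression understates the standard error. The amount cannot be computed, because the number of practitioners serving study families is not given.

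**The case against.** The strongest reply is that the protocol never says agency means will be entered. All employees answer both scales, the readiness questionnaire also covers characteristics of individual staff, and practitioners work in teams, areas or units. Regression does not rule out a multilevel model, and score level and random effects are details that an analysis plan may settle. Figures 2 and 3, to which the analysis section refers, cannot be seen here. This stands in part. A reader might infer that the plan definitely treats three data points as 120, and the text does not support that: the result is conditional on agency scores. What remains goes beyond missing detail. The constructs are organizational, testing is announced, and with agency-level scores no model choice can supply more than three agencies.

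A reader might also infer that any difference between agencies would pass for moderation. That is wrong for the interaction test. Site-wise randomization removes differences in outcome level, and the test is not inflated if the EAS effect is the same in all agencies. Homogeneity is hard to assume, since the agencies differ and the intervention was tailored locally, but the size of the variation is unknown.

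Finally, a reader might infer that the whole of Aim 3 fails. It does not. Fidelity is recorded for each session with each family, child age varies between children, and the main comparison is untouched. Aim 3 is already worded as exploration, although the hypotheses beneath it are announced as tests.

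**Conclusion.** The concern holds in conditional form. The design cannot test readiness or climate as agency-level moderators: one driver leaves 1 df and both leave none. If agency scores are nevertheless used in family-level regression, the nominal 5% interaction test runs at about 5% to 15% for an assumed EAS-effect SD of 0 to 0.3 between agencies. The driver–outcome association in the EAS arm runs at about 7% to 23% for an assumed SD of agency means of 0.1 to 0.3, before baseline adjustment. With practitioner or team scores the problem becomes unmodelled clustering, of unknown size. The degrees of freedom follow from the number of agencies; the error rates rest on the assumed SDs and equal site sizes. The point concerns only the two hypotheses on readiness and climate, and should be dealt with before analysis.

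**What to change.** - State the level at which readiness and climate scores enter the analysis.
- At agency level, show the three site-specific EAS effects with intervals beside each site's readiness and climate scores. Give no p-value for the driver and make no moderation claim.
- If staff surveys can be linked to families, analyse the practitioner's pre-intervention score and its interaction with arm in a mixed model with site fixed effects and a practitioner random intercept. Label it exploratory and associational: practitioners are assigned after randomization, and managers chose who was trained in EAS, so the score may differ by arm for reasons that site effects do not remove.
- Reword the two hypotheses on readiness and climate as exploratory, in line with Aim 3.

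The cost is wording and, where possible, a data linkage. The protocol does not say whether the surveys are identifiable; if they are not, the descriptive report stands alone. Staff turnover may leave some practitioners without a pre-intervention score, and perceived climate is not the same as agency climate. The trial gives up any confirmatory statement about organizational drivers and accepts wider intervals.
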